## Statistical analyses

1. Construct study population. Statistics Denmark has already sampled eczema patients and comparators. However, we need to apply the additional exclusions described above in the section on Study Population.

## Analysis plan

2. Compute summary statistics for covariables (at baseline) and accumulated person-time for exposed (eczema) patients and their comparators (Table 1).

| Table 1. Selected characteristics of eczema patients and matched comparison cohort, Denmark |                        |                          |
|----------------------------------------------------------------------------------------------------|------------------------|--------------------------|
|                                                                                                    | Eczema patients | Comparison cohort |
|                                                                                                    | No. (%)         | No. (%)           |
| Total                                                                                              |                        |                          |
| Age, years                                                                                         |                        |                          |
| Range                                                                                              |                        |                          |
| Median (IQR)                                                                                       |                        |                          |
| Groups                                                                                             |                        |                          |
| <18                                                                                                |                        |                          |
| 18–44                                                                                              |                        |                          |
| 45–64                                                                                              |                        |                          |
| ≥65                                                                                                |                        |                          |
| Sex                                                                                                |                        |                          |
| Women                                                                                              |                        |                          |
| Men                                                                                                |                        |                          |
| Setting for first eczema diagnosis                                                                 |                        |                          |
| Inpatient                                                                                          |                        | –                        |
| Outpatient clinic                                                                                  |                        | –                        |
| Emergency room                                                                                     |                        | –                        |
| Calendar period of index date                                                                      |                        |                          |
| 1982–1999                                                                                          |                        |                          |
| 2000–2004                                                                                          |                        |                          |
| 2005–2009                                                                                          |                        |                          |
| 2010–2016                                                                                          |                        |                          |
| Lifestyle-related diseases                                                                         |                        |                          |
| Chronic obstructive pulmonary disease                                                              |                        |                          |
| Hyperlipidemia or treatment of hyperlipidemia                                                      |                        |                          |
| Hypertension or antihypertensive treatment                                                         |                        |                          |
| Alcohol-related conditions                                                                         |                        |                          |
| Ischemic heart disease                                                                             |                        |                          |
| Hospital-diagnosed obesity                                                                         |                        |                          |
| Diabetes type II                                                                                   |                        |                          |
| Immunosuppression                                                                                  |                        |                          |
| Oral corticosteroids                                                                               |                        |                          |
| Asthma                                                                                             |                        |                          |

## Analysis plan

|                                                             |  |  |
|-------------------------------------------------------------|--|--|
| Educational level*                                          |  |  |
| Short                                                       |  |  |
| Medium                                                      |  |  |
| Long                                                        |  |  |
| Missing                                                     |  |  |
| Partnership status
(married/cohabitating vs.
single)* |  |  |
| Single                                                      |  |  |
| Married/cohabitating                                        |  |  |
| Gross personal income*                                      |  |  |
| Low                                                         |  |  |
| Intermediate                                                |  |  |
| High                                                        |  |  |
| Very high                                                   |  |  |
| Follow-up (years)                                           |  |  |
| Total                                                       |  |  |
| Median (IQR)                                                |  |  |
| Abbreviations: IQR = interquartile range                    |  |  |

\*Educational level, partnership status and gross personal income are presented for those 30 years or older at index date only. To enable interpretation of the categories for gross personal income, we will check the category boundaries for the first and last year of the inclusion period, as well as the mean for the boundaries over the entire study period.

## Analysis plan

3. With time since index date as underlying time scale, we will use stratified Cox regression (conditioning on matched set) to compute unadjusted hazard ratios (99% confidence intervals) to determine associations between eczema and each outcome (that is, comparing eczema patients and the comparison cohort). By stratifying on matched set, the model accounts for birth year, sex and calendar period. We will then fit a “mediation model” additionally adjusting for time-varying lifestyle-related diseases (chronic obstructive pulmonary disease, hyperlipidemia, hypertension, alcohol-related conditions, ischemic heart disease, hospital-diagnosed obesity and type II diabetes). If sufficient power, we will adjust for the lifestyle-related diseases as individual variables.

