## Analysis plan

### *Eczema exposed*

- Persons with a diagnosis of atopic eczema (ICD-8: 691; ICD-10: DL20) in the Danish National Patient Registry between 1 Jan 1977 and 10 February 2018.
- We include all primary and secondary diagnoses for eczema from admissions, hospital outpatient clinics and emergency rooms in the Danish National Patient Registry, including ongoing contacts (that is, persons who at the end of study period are in active follow-up in a hospital outpatient clinic).
- Index date = The earliest hospital record for atopic eczema (date of admission or first outpatient appointment).
- Only persons who are born in Denmark and living in Denmark on the index date (i.e. date of first record for eczema).

For the current study, we will further restrict the study population as follows:

- We will exclude eczema patients (together with their matched comparators) identified by an ICD-8 diagnosis recorded together with an additional (“modification”) code indicating that it potentially an uncertain/unverified/working diagnosis (c\_diagmod=1–7).
- We will exclude patients (together with their matched comparators) with inconsistencies in registration of status and residence in the Civil Registration System (recorded as alive but not living in Denmark but without an emigration date), as we assume that these patients are not living in Denmark and thus not eligible.
- To ensure that we have at least 1 year of registration history from included registries (except the prescription registry), we will only include patients (together with their matched comparators) with index date on 1 January 1982 or later. In the subanalysis on severity and in a sensitivity analysis, we restrict to those diagnosed on 1 January 1996 or later in order to ensure one year of registration history in all databases.
- To ensure at least 1 year of follow-up after start of eligible follow-up (available until 30 June 2017), we will include eczema patients until 30 June 2016.
- We will exclude eczema patients (together with their matched comparators) with a record for any cancer (except non-melanoma skin cancer) before or on index date (see Table 2). That is, we will not only exclude those with history of the cancer outcome of interest. However, in analyses of non-melanoma skin cancer specifically, we will exclude those with previous history of this cancer as well.

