### Covariables

We will include various variables, shown in table 3. With the exception of socioeconomic variables, variables are time-updated. Thus, people will contribute person-time in the unexposed category for a given variable until they fulfill the definition for the condition/treatment, after which they will contribute in the exposed category for the remaining follow-up.

**Table 3.** Covariables

| ICD-8 | ICD-10 | Other codes in patient registry | ATC | Notes |
|-------|--------|---------------------------------|-----|-------|
|-------|--------|---------------------------------|-----|-------|

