## Analysis plan

|                                                                      |                                                                   |                                                                                                                                      |                                                                                                                |
|----------------------------------------------------------------------|-------------------------------------------------------------------|--------------------------------------------------------------------------------------------------------------------------------------|----------------------------------------------------------------------------------------------------------------|
| Age                                                                  | <18
18–44
45–64
≥65 years                                |                                                                                                                                      |                                                                                                                |
| Sex                                                                  | Men
Women                                                      |                                                                                                                                      |                                                                                                                |
| Calendar period                                                      | 1982–1999
2000–2004
2005–2009
2010–2015                  |                                                                                                                                      |                                                                                                                |
| Various lifestyle-related diseases, as proxy for unhealthy lifestyle |                                                                   |                                                                                                                                      |                                                                                                                |

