| Exposed                                                                                |

Estimated hazard ratios from Cox regression with time since index date as underlying timescale, stratified by matched set.

Unadjusted: No adjustment.

Adjusted: Adjusted for baseline educational level, partnership status, income.

Mediation model: Adjusted additionally for time-varying lifestyle-related diseases.

15. We will repeat the main analysis for specific cancers without censoring patients if they develop another individual cancer first.

**Table 15. Number of events, accumulated person-time, and HRs for cancer associated with eczema, Denmark. Analysis without censoring at diagnosis of another specific individual cancer.**

|                                                          |
|----------------------------------------------------------|
| Hazard ratio and 99%
confidence interval  |
|----------------------------------------------------------|

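### No planned hazard ratio adjusts for lifestyle disease at the index date without also adjusting for later disease, so the step to the mediation model cannot be read as mediation

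*Protocol*

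**What the plan says.** The covariable table (Protocol, Covariables, Table 3) groups seven conditions under the label "Various lifestyle-related diseases, as proxy for unhealthy lifestyle": chronic obstructive pulmonary disease (COPD), hyperlipidemia, hypertension, alcohol-related conditions, ischemic heart disease, hospital-diagnosed obesity and type II diabetes.

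On timing, the Covariables section states "With the exception of socioeconomic variables, variables are time-updated". A person counts as unexposed for a condition until its definition is met, "after which they will contribute in the exposed category for the remaining follow-up".

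Statistical analyses, item 3, plans two models. The first is a Cox model stratified on matched set, "to compute unadjusted hazard ratios (99% confidence intervals"; the matched set accounts for birth year, sex and calendar period. The second is described thus: "We will then fit a “mediation model” additionally adjusting for time-varying lifestyle-related diseases".

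Index-date values of the seven conditions appear in item 2 only ("Compute summary statistics for covariables (at baseline"), as descriptive rows of results Table 1. The one results table with a separate adjusted column is Table 14 (item 14), whose footnote reads "Adjusted: Adjusted for baseline educational level, partnership status, income". That analysis is limited to persons aged 30 or older at index.

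**The concern.** The seven diseases have two roles. As proxies for lifestyle before the index date they are candidate confounders of eczema and cancer. As conditions acquired after it they are candidate mediators. The plan gives both roles a single covariate and names the model after the second role only.

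The primary aim asks whether eczema is associated with raised cancer risk. A natural target is the total association net of recorded lifestyle disease at index, with later pathways left open. Neither planned column estimates it: one leaves lifestyle out and the other also closes any later pathway. Lung cancer is the clearest case in the main table. If its HR falls once COPD and the other conditions are added, the column label invites the conclusion that eczema acts through those diseases. The same fall would occur if eczema patients simply had more of them at entry.

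**Working it through.** **Step 1: trace the planned columns.** The protocol states no sample size, event count or expected HR, so there is no figure to reproduce. Results Tables 2 to 17 give:

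- Tables 2 to 7, 9, 12, 13 and 15 to 17: unadjusted, and mediation model with time-varying lifestyle diseases.
- Tables 8, 10 and 11: the same pair, with systemic eczema treatment, immunosuppression or oral corticosteroids added. None of these is among the seven diseases.
- Table 14: a middle column with education, partnership and income, age 30 or older.

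No column fixes the seven diseases at index.

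**Step 2: read the coding.** Under the never/ever rule, a person whose COPD was recorded before index is in the exposed category from the first day of follow-up. A person diagnosed in year 4 moves there in year 4. The mediation model therefore adjusts for index-date disease and later disease through the same term.

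**Step 3: illustrate the consequence.** All inputs here are assumptions: direct eczema HR 1.0; cancer rate r = 0.003 per year; follow-up T = 10 years; one lifestyle disease with prevalence at index 10% in comparators and 10%, 15% or 20% in eczema; disease-cancer HR h = 1.5 or 2.5; new disease at i = 0.02 per year, multiplied by k = 1 or 1.5 in eczema; 10 comparators per patient. Write R = r × h, and use i × k in place of i for eczema. Expected person-years per person are:

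- disease at index: (1 − e^(−RT)) / R
- no disease at index, before onset: (1 − e^(−(r+i)T)) / (r+i)
- no disease at index, after onset: the integral over u from 0 to T of i·e^(−(i+r)u) · (1 − e^(−R(T−u))) / R

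Expected events are the rate (r or R) times person-years. A Poisson model with log person-time offset, fitted to these expected counts, gives:

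| Index prevalence, eczema vs comparators | k | h | Unadjusted | Index-date adjusted | Time-updated |
|---|---|---|---|---|---|
| 10% vs 10% | 1.5 | 1.5 | 1.017 | 1.017 | 1.000 |
| 10% vs 10% | 1.5 | 2.5 | 1.044 | 1.044 | 1.000 |
| 15% vs 10% | 1 | 1.5 | 1.021 | 1.000 | 1.000 |
| 15% vs 10% | 1 | 2.5 | 1.053 | 1.000 | 1.000 |
| 15% vs 10% | 1.5 | 1.5 | 1.037 | 1.016 | 1.000 |
| 15% vs 10% | 1.5 | 2.5 | 1.095 | 1.040 | 1.000 |
| 20% vs 10% | 1 | 1.5 | 1.041 | 1.000 | 1.000 |
| 20% vs 10% | 1 | 2.5 | 1.106 | 1.000 | 1.000 |
| 20% vs 10% | 1.5 | 1.5 | 1.057 | 1.015 | 1.000 |
| 20% vs 10% | 1.5 | 2.5 | 1.145 | 1.037 | 1.000 |

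With 10% vs 10% and k = 1, all three are 1.000. A hand check at the index date for 20% vs 10% and h = 2.5 gives (1 + 0.20 × 1.5) / (1 + 0.10 × 1.5) = 1.30 / 1.15 = 1.130. Averaged over 10 years, as others acquire the disease, this becomes 1.106. A random simulation of the same set-up (200,000 exposed, 2,000,000 unexposed) agreed within 0.015. Matched-set stratification was not modelled.

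**Step 4: compare.** The second row is pure mediation and would print 1.044 and 1.000. The row with 20% vs 10%, k = 1, h = 1.5 is pure confounding and would print 1.041 and 1.000. The planned table could not tell them apart; the index-date-adjusted HR does (1.044 against 1.000). In the last row the total fall is 0.145, of which 1.145 − 1.037 = 0.108, about three quarters, is confounding at index. Across all scenarios the index-date-adjusted and time-updated HRs differ by 0 to 0.044.

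**Step 5: confounding left in the unadjusted HR.** The factor is (1 + p1(RR − 1)) / (1 + p0(RR − 1)). With assumed p0 = 5%:

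| p1/p0 | RR 2 | RR 5 | RR 10 |
|---|---|---|---|
| 1.25 | 1.012 | 1.042 | 1.078 |
| 1.5 | 1.024 | 1.083 | 1.155 |
| 2 | 1.048 | 1.167 | 1.310 |

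This range, 1.01 to 1.31, concerns the unadjusted column only.

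**The case against.** A reader might infer that lifestyle confounding at index goes uncontrolled in the full cohort. The documents do not support that. The never/ever coding carries disease recorded by the index date into the mediation model from day 0, and that model covers the full cohort. In the scenarios without mediation it removed the confounding as completely as an index-date-only model. For the same reason, the socioeconomic column in Table 14 is not the only protection against confounding.

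A second objection is that the two columns bracket the answer, one with the pathway open and one with it closed, and that a third estimand is a preference. Unhealthy lifestyle may also follow from eczema, so treating it as a mediator is defensible. This stands as far as it goes, but the bracket does not say which part of a fall is which, and the model name suggests that it does.

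A third objection is that the added column is not clean either, and this is right. The index date is the first hospital record, so disease present then may follow earlier eczema. A COPD diagnosis after index may reflect smoking before it. Four of the seven definitions (hyperlipidemia, hypertension, alcohol-related conditions, type II diabetes) draw partly on prescriptions, available from 1995, whereas the cohort starts in 1982. The guaranteed one-year history explicitly leaves them out: "To ensure that we have at least 1 year of registration history from included registries (except the prescription registry", in the protocol's words.

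Finally, the document gives none of the inputs for size, and in the assumed scenarios the gap between index-date-adjusted and time-updated HRs is small.

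**Conclusion.** The point holds in a limited form. No planned HR adjusts for lifestyle disease at the index date while leaving later disease unadjusted, so a fall from the unadjusted to the mediation HR cannot be attributed to mediation. The planned HRs can all be computed and none is wrong in itself; the difficulty lies in interpreting the step between them.

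The conclusion rests on the coding rule and the table layouts, not on the illustration. The sizes rest wholly on assumed inputs: a difference of 0 to about 0.04 between the index-date-adjusted and time-updated HRs, and a factor of 1.01 to 1.31 in the unadjusted HR, close to 1 if index prevalence is balanced. The second range is not an error left in the plan as a whole, because the mediation column already adjusts for recorded index-date disease. In persons young at index these diseases may be rare and the extra column may change little; the protocol gives no age distribution.

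**What to change.** Add to results Table 2 a column between Unadjusted and Mediation model, adjusting for the seven diseases fixed at their index-date value, in the three-column layout of Table 14. Repeat it in Table 13, where index dates from 1996 guarantee a year of prescription history.

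State in item 3 and the footnotes that the step from unadjusted to index-date-adjusted is compatible with confounding by recorded lifestyle disease, that the further step to time-varying adjustment is compatible with mediation, and that neither is a clean separation. List the reasons: index-date disease may follow earlier eczema, later disease may mark earlier lifestyle, and prescription-based components are under-recorded for index dates before 1996.

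The cost is one extra model per outcome, 12 in each of the two tables, on variables already derived for Table 1. No new data are needed.
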